### Participants

Participants will be enrolled through two primary channels: (1) newspaper advertisements inviting interested individuals to contact the research team via telephone; or (2) referrals from clinics affiliated with the Hong Kong Hospital Authority. The relevant clinical teams will first contact potential participants, after which the research staff will conduct eligibility screenings. During the initial consultation, a physician (co-investigator) will conduct a detailed clinical history review and comprehensive examination. the PI or a designated co-investigator will furnish potential participants with detailed information regarding the study objectives, methodology, and any risks associated with acupuncture. Written informed consent (Appendix 2: Participant Consent Form) will be obtained prior to participation. Participants will also be informed of their right to withdraw at any point during the study. A total of 150 long COVID patients with neuropsychiatric symptoms will be recruited. The study will be conducted across six Chinese Medicine Research and Clinical Centers of Hong Kong Baptist University. Eligibility criteria are detailed in Table 2.

**TABLE 2 T2:** Inclusion and exclusion criteria.

Inclusion criteria	Exclusion criteria
• Aged 18–80 years.**** • History of SARS-CoV-2 PCR + at least 4 weeks prior; PCR-negative at study entry.**** • At least one persistent neurological symptom (e.g., impaired concentration, headache, sensory disturbances, depression, or “brain fog”) starting around acute COVID-19.**** • Able and willing to consent and complete all assessments and procedures.	• Chronic/remote neurological disorders (e.g., stroke, head trauma, epilepsy, tumor). • Pre-existing intellectual disability. • Cardiovascular diseases (e.g., arrhythmia, heart failure, myocardial infarction, pacemakers). • Acute brain injury or encephalopathy from non-COVID causes (e.g., sepsis, organ failure, drug toxicity). • Documented pre-existing psychiatric illness, including substance abuse. • Open-heart surgery or cardiac arrest within the last 6 months. • Current hospitalization. • Pregnancy.
**Withdrawal criteria**	
• Confirmation of pregnancy during the trial.**** • Discovery of a disease that may affect the trial.**** • Problems with the medical or trial procedures.**** • Other reasons determined by the research team.	

### Participant retention and follow-up

This is a 24 weeks clinical trial, which subjects will need to take 32 sessions of acupuncture treatment and seven regular visits (treatment and follow-up). To bolster participant adherence, we will employ a three-pronged strategy. First, during the informed-consent interview, the research team will review the study timeline, outline possible adverse effects, clarify participant obligations, and provide continuous support and reassurance. Second, a two-week run-in period will screen out ineligible or poorly compliant volunteers before randomization. Third, a dedicated email address ([contact]) and a direct telephone hotline will be activated to ensure prompt, proactive communication and address any participant queries throughout the trial.

### Handling of withdraw and dropout

Participants who meet withdrawal criteria or voluntarily withdraw from the study will have their reasons documented whenever possible. Data collected before withdrawal will be retained for analysis under the intention-to-treat principle unless consent is specifically withdrawn for data usage. Efforts will be made to minimize dropout through proactive follow-ups, flexible scheduling, and continuous communication via the designated email and hotline. Adverse events (AEs) or concerns will be addressed promptly, and any serious issues will be reported to the PI and the ethics committee. Withdrawals and dropouts will be transparently reported in the final study results to ensure data integrity and scientific rigor.

### Interventions

Following baseline assessment, participants randomized to the EAG will receive electroacupuncture stimulation from a registered Chinese Medicine practitioner with more than 5 years of Chinese medicine university education and more than 5 years of clinical experience. A systematic review (45) identified GV20 (Baihui), EX-HN1 (Sishencong), EX-HN3 (Yintang), SP6 (Sanyinjiao), ST36 (Zusanli), ST40 (Fenglong), and LR3 (Taichong) as the most frequently used acupuncture points for cognitive impairment. Accordingly, the rationale for choosing the acupoints is as follows: the acupoints on the head such as GV20 (Baihui) and EX-HN1 (Sishencong) have the local effectof regulating the brain function; the other acupoints on the lower limb, such as LR3 (Taichong) and ST36 (Zusanli), have the effect of soothing liver and strengthening spleenis (46). All acupoint locations adhere to WHO standard definitions (47), specific details of acupoints are summarized in Table 3 and Appendix 3.

**TABLE 3 T3:** Locations of acupuncture points used in electroacupuncture group (EAG).

**Acupoint**	**Location**
Baihui (GV20)	On the top of the head, 7 B-cun directly superior to the posterior hairline, on the anterior median line.
Sishencong (EX-HN1)	Around Baihui (GV20), 1 B-cun anterior, posterior, and lateral to it.
Yintang (EX-HN3)	On the forehead, at the midpoint between the medial ends of the two eyebrows.
Sanyinjiao (SP6)	On the tibial aspect of the leg, posterior to the medial border of the tibia, 3 B-cun superior to the prominence of the medial malleolus.
Zusanli (ST36)	On the anterolateral aspect of the leg, 3 B-cun inferior to Dubi (ST35) and 1 fingerbreadth lateral to the anterior crest of the tibia.
Fenglong (ST40)	On the anterolateral aspect of the leg, 8 B-cun superior to the prominence of the lateral malleolus and two fingerbreadths lateral to the anterior crest of the tibia.
Taichong (LR3)	On the dorsum of the foot, between the first and second metatarsal bones, in the depression distal to the junction of the bases of the two bones, over the dorsalis pedis artery.

EAG: electroacupuncture will be performed using single-use, sterile acupuncture needles with a diameter of 0.20 mm. Needles will be inserted to a depth of 1–3 cm, based on the thickness of local tissue, in accordance with traditional TCM standards. The acupoints are subjected to 2–5 Hz electroacupuncture from an electroacupuncture device (Hwato, Electronic Acupuncture Treatment Instrument, Suzhou Medical Appliance Factory, Jiangsu, China) at an intensity (5–10 mA) that can produce a muscle twitch acceptable to the participant. Each participant allocated to the EAG will undergo 30 min electroacupuncture sessions twice weekly throughout the four-month intervention period (48).SCG: for the sham-control arm, Streitberger’s non-invasive acupuncture needles (Gauge 8 × 1.2/0.30 × 30 mm) will be positioned at non-acupoint sites approximately 0.5 cun from the corresponding acupoints, replicating the same insertion procedure as the acupuncture group (49). Additionally, the needles will be connected to inactive output ports on the electroacupuncture device. The stimulator will emit only the same beeping sound and flashing light continuously, thus producing a “pseudo stimulation” setup that maintains blinding integrity without delivering a therapeutic effect. This sham procedure has been previously validated for both its credibility and its ability to maintain participant blinding (50–54).

### Outcomes measurement

#### Primary outcome

Mini-Mental State Examination (MMSE)

Cognitive function will be evaluated using the Chinese version of MMSE scale (45), which assesses five domains: orientation (up to 10 points), memory (6 points), attention and calculation (5 points), language (8 points), and visuoconstructional ability (1 point). Total scores range from 0 to 30, with 21–24 indicating mild impairment, 10–20 moderate, and below 10 severe. Assessments will be performed at baseline, at weeks 4, 8, 12, and 16 (end of the intervention), and again 2 months after completion of treatment.

Chinese Beck Depression Inventory (CBDI)

Depressive symptoms will be measured using the CBDI, a validated self-reported questionnaire comprising 21 items (maximum total score = 63) (55), with score ranges of 14–19 indicating mild, 20–28 moderate, and above 29 severe depression. Assessments will occur at baseline, at week 4, 8, 12, 16 (end of treatment) and again two months post-intervention.

#### Secondary outcome

Secondary endpoints include the score of ISI (56), BFI-T Form (57), and SF12 (58). All scales are assessed at baseline, at four-week intervals during the 16-week treatment phase (week 4, 8, 12, 16) and again at the 8-week post-treatment follow-up (Table 1). All adverse events will be prospectively recorded, with documentation of their intensity (mild, moderate or severe), duration, outcome, and potential relationship to the study.

### Data management

To ensure impartiality, separate investigators, comprising the data collector, data manager, statistician and outcome assessor, will remain blinded throughout the trial. At week 0 (baseline), participants’ demographic characteristics, symptom severity, medical history, psychological status, and quality of life will be captured via standardized paper questionnaires and electronic surveys. All data will be securely housed on a dedicated network under the supervision of an independent data manager. Two researchers will independently export and assemble the dataset, then perform a cross-verification to confirm completeness and accuracy, any discrepancies will be resolved by a third reviewer referencing the original source documents.

### Data processing and analysis

Descriptive metrics, namely recruitment rates, attrition rates, and treatment adherence, will be reported as count and percentage. All efficacy and safety endpoints will be analyzed under a modified intention-to-treat (ITT) framework. Statistical analyses will be conducted using SPSS for Windows (version 27.0). Statistical significance is defined as a two- sided *P*-value < 0.05. Baseline continuous variables will be expressed as mean ± SD (or median and interquartile range, as appropriate), and categorical variables as frequencies and percentages. Between-group comparisons of normally distributed continuous outcomes will use independent-samples *t*-test, while non-parametric continuous variables will be assessed with Mann-Whitney U test. Categorical data will be evaluated using chi-squared test or Fisher’s exact test. Group differences at weeks 16 and 24 will be tested via analysis of covariance (ANCOVA), adjusting for baseline values. Within-group changes over time will be examined with pair *t*-test for parametric data and Wilcoxon signed-rank test for non-parametric data. Based on the ITT, missing efficacy data will be imputed by last observation carried forward.

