## Methods and analysis

### Trial design and setting

This is a prospective, patient-assessor-blinded, randomized, sham-controlled, multi-center trial designed to examine electroacupuncture’s impact on neuropsychiatric sequelae in long COVID survivors. A total of 150 eligible participants will be allocated in equal numbers to either the electroacupuncture group (EAG) or the sham control group (SCG). Each cohort will complete 32 intervention sessions over a 16 weeks period (2 sessions weekly) and will be followed up for an additional 8 weeks. The primary outcomes will be the changes in the Mini-Mental State Examination (MMSE) and the Chinese Beck Depression Inventory (CBDI) scores before and after treatment. Secondary outcomes will include changes in the Insomnia Severity Index (ISI), Brief Fatigue Inventory-Taiwanese (BFI-T), and the 12-item Short-Form Health Survey (SF-12) scores during the treatment and follow-up periods. These questionnaires (Appendix 1) will be assessed every 4 weeks during both the treatment and follow-up periods. The schedule detailing participant enrolment, intervention administration and outcome assessments are summarized in Table 1, while a flow diagram of the trial design is presented in Figure 1. This trial has been registered in clinicaltrials.gov (NCT05890508) and approved by the Research Ethics Committee of Hong Kong Baptist University (REC/21-22/0467).

**TABLE 1 T1:** Schedule for outcome measurement.

Period	B	T																F	
**Visit**	**1**				**2**				**3**				**4**				**5**	**6**	**7**
**Week**	**0**	**1**	**2**	**3**	**4**	**5**	**6**	**7**	**8**	**9**	**1** **0**	**1** **1**	**1** **2**	**1** **3**	**1** **4**	**1** **5**	**1** **6**	**2** **0**	**2** **4**
General assessment	√																		
Screening for enrolment	√																		
Treatment (acupuncture/sham-acupuncture)	Twice a week (16 week treatment)																		
MMSE	√				√				√				√				√	√	√
CBDI	√				√				√				√				√	√	√
ISI	√				√				√				√				√	√	√
SF12	√				√				√				√				√	√	√
Adverse event report	As needed																		

B, baseline; T, treatment phase; F, follow-up phase; MMSE, Mini-Mental State Examination; CBDI, Chinese Beck Depression Inventory Fast Screen; ISI, Insomnia Severity Index; SF12, the Short Form 12.

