### Sample size

The target sample size was determined by reviewing prior trials using MMSE and BDI to assess the effectiveness of acupuncture versus sham treatment. The observed differences in MMSE and BDI scores between groups were 2.82 and 3.96 points, respectively (39, 40). Based on effect sizes of 0.76 for MMSE and 0.75 for BDI, the BDI-based between-group difference was smaller and was therefore selected for estimation of sample size to yield a more conservative result. To control the overall type I error and ensure sufficient statistical power, the following parameters were applied: a two-sided α level of 0.025 (Bonferroni correction), a power of 0.8, and an equal allocation ratio (1:1) between the acupuncture and sham acupuncture groups. Under these assumptions, the calculation yielded a requirement of 36 subjects per arm. Allowing for an anticipated 20% dropout rate, the target total sample size was adjusted to 90 cases. To increase robustness and ensure an adequate sample reserve for future subgroup analyses, we plan to recruit 150 participants (41–44). Sample size estimation was conducted using G*Power (Version 3.1).

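### The two primary outcomes are planned at two-sided 0.025 each, but the analysis section judges every test at 0.05, which roughly doubles the intended 5% familywise error

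*Protocol article*

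**What the plan says.** The protocol article names two primary outcomes under Trial design and setting: "The primary outcomes will be the changes in the Mini-Mental State Examination (MMSE) and the Chinese Beck Depression Inventory (CBDI) scores before and after treatment".

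The Sample size section introduces its design parameters with the words "To control the overall type I error and ensure sufficient statistical power, the following parameters were applied", and the first of them is "a two-sided α level of 0.025 (Bonferroni correction), a power of 0.8". With a standardised effect of 0.75 it arrives at 36 per arm, 90 in total after 20% dropout, and a recruitment target of 150.

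The Data processing and analysis section places all efficacy and safety endpoints in one framework and gives a single threshold: "Statistical significance is defined as a two- sided *P*-value < 0.05". It mentions neither the Bonferroni level nor a separate rule for MMSE and CBDI. On time points it says: "Group differences at weeks 16 and 24 will be tested via analysis of covariance (ANCOVA), adjusting for baseline values". The article nowhere names a primary time point.

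**The concern.** The alpha entered in a sample size calculation does not itself control error. Only the rule applied to the data does. The article sizes the trial for one rule and states another. With p = 0.03 on MMSE, the trial would be positive under the analysis section and not under the Sample size section. Which reading applies would then be settled after the result is known, which is what pre-specification is meant to prevent. If the analysis section is followed, a false claim of benefit on cognition or depression is about twice as likely as the planning level intends.

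**Working it through.** **Inputs.** From the Sample size section: two-sided alpha 0.025, power 0.80, 1:1 allocation, standardised effects of 0.76 (MMSE) and 0.75 (BDI, the one used), 36 per arm, 20% dropout, totals of 90 and 150. From the analysis section: two-sided 0.05, with tests at weeks 16 and 24. The documents give no correlation between outcomes or between weeks, so all correlations below are assumptions.

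**Step 1: reproduce the plan's own figure.** Two-sample t-test, noncentral t, with noncentrality d × √(n/2) and 2n − 2 degrees of freedom.

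- d = 0.75, two-sided 0.025: n = 36 per arm (noncentrality 0.75 × √18 = 3.18, power 0.811). With 35 per arm, power is 0.799.
- d = 0.75, two-sided 0.05: n = 29 per arm (power 0.801).
- Dropout: 72 / (1 − 0.20) = 90.

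The stated 36 and 90 are correct, and the 36 rests on 0.025. The sizing arithmetic is not at fault.

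**Step 2: familywise error with two primary outcomes at 0.05, either one sufficient.**

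- Independent: 1 − (1 − 0.05)² = 1 − 0.9025 = 0.0975. The Bonferroni bound is 2 × 0.05 = 0.10.
- Assumed correlation 0.3: about 0.095. Assumed correlation 0.5: about 0.091. Both come from simulating correlated normal test statistics (1 million draws).

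**Step 3: the same with the planned level.** At 0.025 each and one time point: 1 − (1 − 0.025)² = 1 − 0.950625 = 0.0494 if independent, with a bound of 2 × 0.025 = 0.05.

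**Step 4: conditional scenario, only if weeks 16 and 24 were both confirmatory.** Four tests at 0.05, by the same simulation:

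| Between-outcome correlation (assumed) | Between-week correlation 0.5 | 0.7 | 0.8 |
|---|---|---|---|
| 0 | 0.173 | 0.161 | 0.150 |
| 0.3 | 0.169 | 0.157 | 0.146 |
| 0.5 | 0.161 | 0.149 | 0.139 |

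The range is about 14% to 17%. Under the same assumptions, four tests at 0.025 would give about 7.4% to 9.0%. Restoring 0.025 therefore holds the error at 5% only if one time point is named as primary.

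**Step 5: power cost of keeping 0.025.** 150 × 0.80 / 2 = 60 per arm. At d = 0.75, power is 0.983 at 0.05 and 0.966 at 0.025.

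**The case against.** **The 0.05 is a blanket convention.** One can read it as the usual sentence for baseline, safety, within-group and secondary tests, or as the overall 5% that the Sample size section divides by two. A statistical analysis plan that is not shown may also carry the detail. This has some force: the article declares its intention to correct, so a reader should not infer that the trial has abandoned multiplicity control. It does not remove the conflict. The sentence is unrestricted, and the same paragraph covers all efficacy endpoints and the ANCOVA. The point is not that detail is missing. Two stated thresholds disagree, and no later document can agree with both.

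**Both outcomes must succeed.** Under that rule 0.05 each would be acceptable. The article states no such rule, and a Bonferroni split would serve no purpose under it.

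**The stronger reading: four confirmatory tests.** A reader might infer four primary tests (two outcomes at two weeks) and an error of 1 − 0.95⁴ = 18.5%, nearly four times the intended level. The documents do not support this. The Trial design and setting section defines the primary outcomes as pre- to post-treatment changes. It contrasts them with secondary outcomes followed through treatment and follow-up. Treatment ends at week 16, so that week is the natural primary time point. The ANCOVA sentence names no outcome and does not call week 24 primary. The 18.5% also requires independent tests. The same scale in the same patients will be correlated across weeks, and more so under last observation carried forward, because someone lost after week 16 contributes the same value at both. What remains is imprecision: no section names the primary time point, and the Outcomes measurement section lists the two-month post-treatment assessment under each primary outcome.

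**Conclusion.** The contradiction between 0.025 and 0.05 stands. Applying the analysis section as written gives a familywise error of 9.75% if the outcomes are independent, and about 9.1% to 9.5% at assumed correlations of 0.5 to 0.3, against an intended 5%. This rests on either outcome alone being able to support a claim, which the Bonferroni correction implies, and on week 16 as the single primary time point, which the text suggests without saying so. The 14% to 17% range applies only if both weeks were treated as confirmatory and should be cited only with that condition.

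**What to change.** In Data processing and analysis, state that:

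- week 16 is the primary time point;
- MMSE and CBDI change from baseline to week 16 are each tested at two-sided 0.025, or by Holm at overall two-sided 0.05;
- week 24 is supportive;
- the 0.05 level applies only to the other, non-confirmatory tests.

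The cost is a short addition to the text and a slightly stricter threshold for each primary outcome. At d = 0.75 with 60 per arm, power falls from 0.983 to 0.966. The planned 150 participants suffice.

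### Baseline adjustment is named only for weeks 16 and 24; the interim visits have no named baseline-adjusted group comparison, a modest and cheaply avoided loss of precision for the secondary questions

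*Protocol article*

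**What the plan says.** The Data processing and analysis section of the Protocol article gives three methods for continuous outcomes.

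- A general between-group method: "Between-group comparisons of normally distributed continuous outcomes will use independent-samples" t-tests, with Mann-Whitney as the non-parametric alternative. No visit is named, and the text does not say whether raw scores or changes are compared.
- A baseline-adjusted method for two visits: "Group differences at weeks 16 and 24 will be tested via analysis of covariance (ANCOVA), adjusting for baseline values".
- A method over time, within each arm: "Within-group changes over time will be examined with pair" t-tests, or Wilcoxon signed-rank tests.

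No between-group model across visits is stated. The Trial design and setting section defines the secondary outcomes as changes in "scores during the treatment and follow-up periods" and says that the questionnaires "will be assessed every 4 weeks during both the treatment and follow-up periods". Table 1 accordingly shows weeks 4, 8, 12, 16, 20 and 24 after baseline.

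The outcome sections give a shorter list. For the MMSE it is "at baseline, at weeks 4, 8, 12, and 16 (end of the intervention), and again 2 months after completion of treatment". For the secondary scales it is "week 4, 8, 12, 16) and again at the 8-week post-treatment follow-up (Table 1". Neither includes week 20.

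**The concern.** The secondary outcomes cover the treatment and follow-up periods, yet the adjusted comparison is placed only at the end of each. For the visits in between, a reader cannot tell which between-group comparison applies, and none that is named uses the baseline value as a covariate. The method attached to change over time is the paired within-arm test. A within-arm change mixes treatment effect with natural recovery and non-specific response, so it cannot show when electroacupuncture and sham separate.

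The baseline value of each scale is collected anyway. Leaving it out of the interim comparisons gives wider confidence intervals than the same data would support, so a moderate early difference could be missed. This would hold with complete data and does not depend on how missing values are treated.

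**Working it through.** **1. Visits affected.** Design section and Table 1: six post-baseline visits (4, 8, 12, 16, 20, 24), less two with ANCOVA, leaves four (4, 8, 12, 20). Outcome sections: five post-baseline visits (4, 8, 12, 16, 24), less two, leaves three (4, 8, 12). Weeks 4, 8 and 12 are affected on either reading.

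In scale assessments the upper bound is 150 × 4 visits × 5 scales = 3,000. Without week 20 it is 150 × 3 × 5 = 2,250. Table 1 has no row for the BFI-T; with its four scales at four visits the count is 150 × 4 × 4 = 2,400.

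**2. The plan's own figure.** The Sample size section uses d = 0.75, two-sided alpha 0.025, power 0.80 and 1:1 allocation. A two-sample t-test with the noncentral t gives 35.08, rounded up to 36 per arm; 36/0.80 = 45 per arm, 90 in total. Both stated figures reproduce. They do not depend on which visits get ANCOVA.

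**3. Inputs for the efficiency comparison.**
- SD implied for the CBDI: 3.96/0.75 = 5.28 (Sample size section), taken to apply at each visit.
- 60 per arm: 75 less the planned 20% dropout.
- Correlation r between baseline and follow-up score: not in the documents; assumed 0.4 to 0.7.
- Two-sided alpha 0.05 (Data processing and analysis section).
- Effect: d = 0.75 (planning value) and d = 0.5 (assumed, for a smaller interim effect).

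**4. Formula.** SE = SD × √(2/n) × √f, with f = 1 for a raw-score test, 2(1 − r) for a change-score test and 1 − r² for ANCOVA. Here 5.28 × √(2/60) = 0.96.

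| Comparison | f at r = 0.4 | f at r = 0.7 | SE at r = 0.4 | SE at r = 0.7 |
|---|---|---|---|---|
| Raw score | 1.00 | 1.00 | 0.96 | 0.96 |
| Change score | 1.20 | 0.60 | 1.06 | 0.75 |
| Baseline-adjusted | 0.84 | 0.51 | 0.88 | 0.69 |

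**5. Gain in effective sample size from adjustment.**
- Over the raw score: 1/0.84 = 1.19 to 1/0.51 = 1.96, that is 19% to 96%.
- Over the change score: 1.20/0.84 = 1.43 to 0.60/0.51 = 1.18, that is 43% down to 18%.

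**6. Power (noncentral t, effect d/√f, 60 per arm).**

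| Effect | Raw score | Change score, r = 0.4 to 0.7 | Adjusted, r = 0.4 to 0.7 |
|---|---|---|---|
| d = 0.75 | 98.3% | 96.1% to >99.9% | 99.4% to >99.9% |
| d = 0.5 | 77.5% | 69.8% to 93.9% | 84.2% to 96.7% |

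Against the raw-score test, adjustment adds 1 to 2 points at d = 0.75 and 7 to 19 points at d = 0.5. Against the change-score test at d = 0.5 it adds 14 points at r = 0.4 and 3 points at r = 0.7.

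**The case against.** The strongest defence is that the endpoints that matter are covered. The primary outcomes are MMSE and CBDI changes from before to after treatment, and week 16 is the end of treatment and has ANCOVA. Week 24 closes follow-up and has it too. Confining adjusted tests to those two visits is a reasonable way to limit multiplicity, and the handling of interim visits may be set out in an analysis plan not shown. This stands as far as the primary conclusion goes. It does not fully answer the point, because the article does not call the other visits descriptive. It gives a general between-group test and a 0.05 threshold with no limit by visit, and it ties change over time to within-arm tests.

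A reader might infer that the interim visits get at best an unadjusted test. The text does not establish that. The outcomes are defined as changes, and a t-test on change scores uses baseline, though less efficiently than ANCOVA. A reader might also infer that an unadjusted comparison would be invalid. Under randomisation it keeps its type I error; what is lost is precision.

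The size also depends on assumptions. The documents give neither r nor an effect of 0.5, and at the planning effect the loss is small. Using 60 per arm applies the full dropout from week 4. The plan says that "missing efficacy data will be imputed by last observation carried forward", so the number analysed may be nearer 75 per arm. With 75, power at d = 0.5 is 86% for the raw score against 91% to 99% adjusted, a gain of 5 to 13 points.

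**Conclusion.** The point holds as a minor one. Weeks 4, 8 and 12, and week 20 if it is assessed, have no named baseline-adjusted group comparison, and the one method tied to change over time estimates no treatment effect. The cost is precision for the outcomes defined over the treatment and follow-up periods: 19% to 96% in effective sample size against a raw-score test, or 18% to 43% against a change-score test, if r lies between 0.4 and 0.7. In power this is negligible at d = 0.75 and matters only for smaller effects.

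It is not an error in the primary analysis, and the documents do not support reading it as one: the week-16 and week-24 contrasts are already adjusted. Whether four of six or three of five visits are concerned cannot be settled until the two assessment schedules are reconciled.

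**What to change.** For each scale, extend the baseline adjustment to every scheduled visit. One way is a single repeated-measures model with group, visit, group-by-visit, baseline and baseline-by-visit terms and an unstructured covariance, which the mixed-model procedure of the named software can fit. Keep the week-16 contrast in its present role; with complete data it equals the planned ANCOVA. Report the group difference with its confidence interval at each interim visit, labelled supportive, and present within-arm changes as description only. Reconcile the design section and Table 1 with the outcome sections on whether week 20 is assessed.

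The cost is a few lines in the analysis section, with no new data and no extra patients. The downside is more secondary estimates to report: 3 or 4 interim visits × 5 scales = 15 or 20, which is why they need the supportive label.
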